### Study population and inclusion/exclusion criteria

Subject are recruited from their primary care practitioner if they have a diagnosis of diabetes with a GAD antibody result of 101 WHO units or more.

#### Inclusion criteria

1. Male, non-fertile female (i.e., post menopausal, post hysterectomy, or sterilized by tubal ligation) or female of childbearing potential using a medically approved birth control method.

2. The patient has a diagnosis of diabetes mellitus according to WHO classification.

3. The patient has a positive GAD antibody test of 101 WHO units or more on two separate occasions.

4. Age 18 +

5. The patient did not start on insulin within 1 month of diagnosis

6. Written informed consent to participate in the study.

7. Ability to comply with all study requirements.

#### Exclusion criteria

1. Pregnant or breast-feeding females and females who plan pregnancy or breast-feeding during the course of the study.

2. A history of:

▪ Diabetes that is a result of pancreatic injury, or secondary forms of diabetes, e.g., Cushing's syndrome and acromegaly.

▪ Acute metabolic diabetic complications such as ketoacidosis or hyperosmolar state (coma) within the past 6 months

3. Acute infections, which may affect blood glucose control within 4 weeks prior to visit 1.

4. Malignancy including leukaemia and lymphoma (not including basal cell skin cancer) within the last 5 years.

5. The patient has a known immune deficiency from any disease, or a condition associated with an immune deficiency.

6. The patient is receiving immunosuppressive or immunomodulating agents or cytotoxic therapy, or any medication that, in the opinion of the site investigator, might interfere with the study.

7. Any of the following significant laboratory abnormalities:

• Patients with severe renal failure as defined previous renal transplant or currently having renal dialysis or GFR < 30.

• Clinically significant laboratory abnormalities, confirmed by repeat measurement, that may interfere with the assessment of safety and/or efficacy of the study drug, other than hyperglycemia and glycosuria at visit 1.

• Severe ketonuria (+++ on urine sticks testing; ++ on repeated urine sticks testing).

8. The patient is a known or suspected drug abuser.

9. The patient has chronic hepatitis or liver cirrhosis, or any other chronic liver disease.

10. The patient is known to test positive for hepatitis B antigens or hepatitis C antibodies

11. The patient is known to test positive for HIV antibodies.

12. The patient has any significant diseases or conditions, including psychiatric disorders and substance abuse that, in the opinion of the site investigator, are likely to affect the patient's response to treatment or their ability to complete the study.

13. The patient has chronic haematological disease.

14. The patient has had a severe blood loss (≥ 400 mL, e.g., blood donation) within 2 months before the first dosing of the study medication.

15. The patient has known proliferative retinopathy.

16. Patient has had stage 3–4 heart failure.

17. The patient is participating in another research study which may affect the results of this trial.

### Withdrawn from study

A patient is considered to have withdrawn from the study if they completely withdraw from the study, i.e.:

- Move and do not provide a new address or contact number

- Miss more than 3 visits without contacting the study centre.

- Die

However, if they discontinue treatment but continue participate in data collection they will not be considered to have withdrawn, i.e:

- Want to change therapy due to personal reasons but attend a termination visit.

- Experience a serious adverse event that in the medical judgement of the site investigator and for the best interest of the subject, are grounds for discontinuation, but attend a termination visit.

- Withdraw consent but give consent to the use of the data collected to date.

- Develop a concomitant condition which is given in the exclusion criteria but do attend a termination visit.

If a patient discontinues the study prematurely at any time after entering the study, attempts should be made to conduct a termination final visit at which time all of the assessments listed for the final visit will be performed.

The reason for premature discontinuation and – if applicable – the final visit will be documented.

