### Analysis plan

The statistical evaluation will be performed using SPSS. All data will be listed and trial summary tables will be provided. Summary statistics will be presented by group.

The primary analysis will be an intention to treat analysis examining (1) the average change in C peptide level at the end of the study in both groups and (2) the average change in HbA1c level at the end of the study in both groups. A linear regression model will be used to examine the effect of baseline GAD level, age, sex and baseline fasting C-peptide or HbA1c level as covariate and a treatment term on the change in HbA1c and C-peptide levels. In addition, repeated measures analysis (area under the curve, maximum minus minimum, time taken to maximum, time taken to minimum and slope) for C-peptide and HbA1c will be performed. ANOVA for repeated measurements with be used when variables are normally distributed. Otherwise, log transformations or non parametric tests will be employed.

Data will be collected by research nurses under the medical care of [name] and [name] and monitored by the trial co-ordinator. The analysis will be performed by [name] who will be blind to treatment group until after all analysis has been completed and interpreted. The CONSORT statement will be followed and used for reporting results.

Secondary analysis will include: Intention to treat analysis of :

(1) Average change in fasting C-peptide level in the insulin group compared to the control (best alternative care) group at 12 months.

(2) Average change in HbA1c level in the insulin group compared to the standard care group at 12 month. Data will be presented using confidence intervals only.

(4) Quality of life in the insulin vs standard care groups

(5) Number of events of fasting glucose being above 8 in the insulin vs standard care arm.

(6) Proportion of patients with a C-peptide below 0.38 ng/ml at baseline, 12 months and 24 months.

(7) Level of inflammatory markers in the insulin vs standard care arm

(8) GAD levels of insulin vs standard care

(9) Episodes of adverse events in the insulin vs standard care arms

(10) Weight gain in terms of BMI and waist/hip ratio in both groups

(11) HOMA or insulin resistance in both groups

We shall use two sided tests and confidence intervals for all comparisons.

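### Patients who stop allocated treatment are counted as still in data collection, but the text ties that to a single termination visit, so they may have no month-24 value for the intention-to-treat comparison

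*Protocol article*

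**What the plan says.** All quotes here are from the protocol article.

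- **Rule (Withdrawn from study).** "However, if they discontinue treatment but continue participate in data collection they will not be considered to have withdrawn".
- **Cases that count as not withdrawn.** There are four, introduced by i.e. Three end in a termination visit: a personal wish to change therapy ("Want to change therapy due to personal reasons but attend a termination visit"), a serious adverse event whose circumstances "are grounds for discontinuation, but attend a termination visit", and a new excluded condition ("Develop a concomitant condition which is given in the exclusion criteria but do attend a termination visit"). The fourth involves no further data: "Withdraw consent but give consent to the use of the data collected to date".
- **Termination visit (same section).** For a patient who leaves the study early, "attempts should be made to conduct a termination final visit at which time all of the assessments listed for the final visit will be performed".
- **Follow-up procedure.** Visits are 3-monthly after randomisation. The section does not mention patients who are off allocated treatment.
- **Analysis plan.** "The primary analysis will be an intention to treat analysis" of average change in C-peptide and HbA1c at the end of the study. The Primary objectives set the period at 24 months.
- **Handling of missing and incomplete data.** The last recorded value is used if data are judged missing at random; otherwise best-case and worst-case values are compared. Missing laboratory values may be sought from GP-linked records unless the patient has refused this.

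**The concern.** The governing sentence describes people who go on providing data, but the cases listed under it describe people who are leaving. A site that follows the list would do one early visit with the final-visit assessments and then stop. No sentence says that the 3-monthly visits or the month-24 visit continue after allocated treatment is stopped.

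An intention-to-treat comparison of change over 24 months needs month-24 outcomes from everyone randomised who still consents, whatever treatment they are on. A value taken at, say, month 6 answers a different question.

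Time matters in this disease. The Background describes LADA as progressing slowly to insulin dependence, so C-peptide is expected to fall, and an early value used as final would tend to flatter the arm with more or earlier exits. The arms also differ in how a patient can exit. Tablet patients have several onward steps inside their strategy, whereas a patient who stops insulin in the insulin arm has none. Treatment is open, so preference can play a part. Unequal stopping is therefore plausible, though the documents do not show that it will occur.

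**Working it through.** **1. Where an early leaver's data go**

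| Route | Value used for month 24 |
|---|---|
| Termination visit accepted as the final visit | Early value |
| Treated as missing, judged missing at random | Last recorded value, which is the termination value if there is one |
| Treated as missing, judged not at random | Best-case and worst-case values |
| Laboratory record found through the GP | A later value, if a test was done and access was not refused |

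Only the last route can give an observed month-24 value. It is only an attempt, and nothing in the article says that fasting C-peptide is measured outside the trial.

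**2. Bias under the first two routes**

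Let p be the proportion of an arm leaving early, and d the mean HbA1c rise between the termination visit and month 24. Using termination values understates that arm's month-24 mean by p × d. The between-arm difference is therefore shifted by

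p(insulin) × d(insulin) − p(tablet) × d(tablet).

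The documents give neither p nor d, so the values below are assumptions, with the same d in both arms.

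- Equal stopping: (p − p) × d = 0.
- 20% versus 5%, d = 0.5: 0.15 × 0.5 = 0.075 points, and 0.075/0.7 = 11% of the target.
- 20% versus 5%, d = 1.0: 0.15 × 1.0 = 0.15 points, 21% of the target.
- 20% versus 5%, d = 1.5: 0.15 × 1.5 = 0.225 points, 32% of the target.
- Stopping in one arm only, d = 0.5 to 1.0: 0.05 to 0.10 points at 10% stopping, and 0.10 to 0.20 at 20%.

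If HbA1c rises later and the insulin arm has more leavers, the shift favours insulin. If the tablet arm has more, the sign reverses.

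The formula is the same for fasting C-peptide. With the same imbalance, a later fall as large as the 0.2 nmol/l target difference would shift the comparison by 0.15 × 0.2 = 0.03 nmol/l. The documents give no rate of fall.

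**3. Precision**

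The plan's sample size, read as per arm, reproduces: 2 × [1.5 × (1.960 + 1.282)/0.7]² = 96.5, rounded up to 97. Power at 97 is 90.1%. If 10% or 20% of 97 per arm had no month-24 value and were left out, HbA1c power would be 86.9% or 82.8%. The plan states 97 as analysable patients, so this shows only what lost outcomes cost. The point does not rest on it.

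**The case against.** The strongest reply is that a single visit is inferred, not stated. The governing sentence speaks of people who keep contributing data. The termination-visit paragraph is triggered by leaving the study, which is a different event from stopping treatment. Follow-up procedure makes no exception for patients off treatment, and the visit schedule (Figure 3) could not be checked. This stands as a limit on confidence: later visits are not forbidden. It does not remove the problem, because the list equates continued data collection with the termination visit, and sites could reasonably act on that.

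Several stronger readings are tempting, and the documents do not support them.

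- **The early value always becomes the final value.** The last-value rule is conditional. Arm-related stopping is the kind of missingness that the best-case and worst-case branch is meant for, and record retrieval may recover some values.
- **Any change of tablet treatment ends follow-up.** It does not. Metformin intolerance leads to Step 3, and adverse events suggestive of heart disease on rosiglitazone lead to Step 4. Both lie within the allocated strategy. Only changes outside it, or serious adverse events judged grounds for discontinuation, are at issue.
- **Attrition will be under-reported.** Reasons for discontinuation are to be documented and CONSORT is to be followed. No passage removes withdrawn patients from the intention-to-treat analysis. Counting withdrawn consent as not withdrawn is a misleading label that should be corrected, but it adds no bias by itself.

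It is also fair to object that the stopping rates are invented. They are, so the range has to include zero.

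**Conclusion.** The section contradicts itself, and on its natural reading it leaves patients who stop allocated treatment without a planned month-24 outcome. That conflicts with an intention-to-treat comparison over 24 months. A reader might go further and infer that the primary estimate becomes mostly an on-treatment one. That does not follow, since neither the number of such patients nor the end of their follow-up is established.

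The bias cannot be sized from the documents. It is zero if stopping and later drift are equal between arms, and about 0.08 to 0.23 HbA1c points under the assumed 20% versus 5% stopping with 0.5 to 1.5 points of drift. Those figures assume that every leaver's termination value is used, that drift is the same in both arms, and that no records are retrieved. This should be fixed. Confidence is moderate, because the single-visit reading is inferred.

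**What to change.** - State that stopping or changing allocated treatment is not the same as leaving follow-up.
- Keep every randomised patient who still consents on the existing 3-monthly schedule to month 24, whatever treatment they receive. At minimum, obtain fasting C-peptide and HbA1c at month 24.
- Use a termination visit only when a patient leaves the study, and analyse its values at their actual date, not as month 24.
- Class withdrawal of consent to further follow-up as withdrawal, and record separately whether data already collected may be used.
- Say explicitly that planned tablet-arm steps, including Step 4 insulin, are not discontinuation of allocated treatment.
- Where a month-24 visit is missed, apply the laboratory-record retrieval already provided for.

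The cost is a short amendment and modest extra follow-up effort on a schedule that already exists. Some patients will decline, so some month-24 values will still be missing.

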### Follow up procedure

Patients are seen for a screening visit where they are asked to give consent and have baseline tests regarding inclusion/exclusion criteria. They return after 2 weeks for randomisation and are followed every 3 months there after. [See Figure 3]

**Figure 3 F3:**
[figure not shown]
Schedule of visits.

### Analysis plan

The statistical evaluation will be performed using SPSS. All data will be listed and trial summary tables will be provided. Summary statistics will be presented by group.

The primary analysis will be an intention to treat analysis examining (1) the average change in C peptide level at the end of the study in both groups and (2) the average change in HbA1c level at the end of the study in both groups. A linear regression model will be used to examine the effect of baseline GAD level, age, sex and baseline fasting C-peptide or HbA1c level as covariate and a treatment term on the change in HbA1c and C-peptide levels. In addition, repeated measures analysis (area under the curve, maximum minus minimum, time taken to maximum, time taken to minimum and slope) for C-peptide and HbA1c will be performed. ANOVA for repeated measurements with be used when variables are normally distributed. Otherwise, log transformations or non parametric tests will be employed.

Data will be collected by research nurses under the medical care of [name] and [name] and monitored by the trial co-ordinator. The analysis will be performed by [name] who will be blind to treatment group until after all analysis has been completed and interpreted. The CONSORT statement will be followed and used for reporting results.

Secondary analysis will include: Intention to treat analysis of :

(1) Average change in fasting C-peptide level in the insulin group compared to the control (best alternative care) group at 12 months.

(2) Average change in HbA1c level in the insulin group compared to the standard care group at 12 month. Data will be presented using confidence intervals only.

(4) Quality of life in the insulin vs standard care groups

(5) Number of events of fasting glucose being above 8 in the insulin vs standard care arm.

(6) Proportion of patients with a C-peptide below 0.38 ng/ml at baseline, 12 months and 24 months.

(7) Level of inflammatory markers in the insulin vs standard care arm

(8) GAD levels of insulin vs standard care

(9) Episodes of adverse events in the insulin vs standard care arms

(10) Weight gain in terms of BMI and waist/hip ratio in both groups

(11) HOMA or insulin resistance in both groups

We shall use two sided tests and confidence intervals for all comparisons.

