#### Primary objectives

To examine the effect of standard treatment for type 1 (insulin [NovoMix 30] therapy) compared with standard treatment for type 2 diabetes (tablets), on (1) change in fasting serum C-peptide level over 24 months and (2) change in HbA1c level over 24 months in patients with LADA.

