**Figure 2 F2:**
[figure not shown]
Standard treatment arm.

Patient's not treated with tablets will be given a 3 months trial of lifestyle modification including advice on diet, exercise and smoking. If HbA1_c _remains at 7% or above the patient will progress to step 2. Patients will be progressed to step 2 if their GP has already put them on metformin (put in at number of metformin tables that GP has recommended) or sulphonylurea or if their baseline HbA1_c _is above 8% (patients will start on one 500 mg tablet per day). This means that sulphonylurea will be discontinued in all patients. Patients on step 1 will be progressed to step 2 before the 3 month period if they have already had a 3 month period of diet before starting the study AND during phone contact they report to be symptomatic (thirst, fatigue, polyuria) and unwell. In these cases, patients may be invited to attend clinic before the 3 month period to be given metformin.

##### Step 2

Life style modification and Metformin. If the patient has a HbA1_c _of 7%–7.5% they start on 500 mg × 1 per day for the next 3 months. If the HbA1_c _is 7.6%–8.0% they would start the first week on 500 mg × 1 day and then for the remaining period of the three months will take 500 mg × 2 day. If the HbA1_c _is above 8.0% then patient will be on 500 mg × 3 per day. This will be titrated at the rate of 500 mg × 1 for the first week, 500 mg × 2 for the second week and 500 mg × 3 for the remaining time of the 3 month period. If unable to tolerate metformin then the participant will be given Glucophage SR and if unable to tollerate this they will then progress to Step 3. If HbA1_c _remains at 7% or above then those on 1 tablet per day will be moved to 2 tablets per day, those on 2 tablets per day will be moved to 3 tablets per day, those on 3 tablets per day will be move to maximum dose of 2 gms per day. If after 3 months the HbA1_c _is above 7% even with maximum dose, then progress to Step 3. If during telephone contact the patient report symptoms then they may be titrated up. In summary, patients will be have their HbA1c evaluated every 3 months and will be titriated accordingly.

##### Step 3

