### Sample size

The study conducted in China [14] examined fasting C-peptide levels over 12 month, the average difference in C-peptide at 12 months was 0.18 nmol/l (stdev: 0.5 nmol/l) between the insulin vs the SU groups. To find a difference of 0.7% in average HbA1c (standard deviation = 1.5%) we would need 97 analysible people in the insulin and the standard care arms of the study (power 90%, significance = 5%). This would detect an average difference of 0.2 nmol/l in fasting C-peptide. As the power calculation is based on patients in China, we will re-calculate the sample size based on the standard deviation of the first 30 patients recruited in our study. We will examine the standard deviation of the HbA1c and the fasting C-peptide in all 30 patients at 3 months (regardless of treatment) in order to re-estimate the sample size assuming a difference of 0.7% in HbA1c and 0.2 nmol/l in fasting C-peptide.

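### Optional precision gain: each primary regression carries only one of the two outcome baselines and no term for diabetes treatment at entry, although these values are to hand before randomisation

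*Protocol article*

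**What the plan says.** The Primary objectives name two outcomes, "change in fasting serum C-peptide level over 24 months and (2) change in HbA1c level over 24 months". The Analysis plan analyses each by linear regression with "baseline GAD level, age, sex and baseline fasting C-peptide or HbA1c level as covariate and a treatment term". So each model has a treatment term, three common covariates (GAD level, age, sex) and an outcome baseline. The word *or* is most naturally read as the baseline of the outcome being modelled.

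Both laboratory baselines are needed for the changes themselves, so both exist for every patient who can be analysed. Treatment at entry is not listed as a baseline variable. It must nevertheless be known, at least in the tablet arm, because Step 1 acts on it: "Patients will be progressed to step 2 if their GP has already put them on metformin", and likewise for sulphonylurea, followed by "This means that sulphonylurea will be discontinued in all patients". The abstract excludes insulin at entry, so patients enter on diet alone or on non-insulin treatment.

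**The concern.** The article itself gives reasons to expect the omitted values to be prognostic. The Background treats C-peptide response as a measure of beta-cell function and links sulphonylurea use to depleted insulin reserves and poorer fasting glucose. The Secondary objectives define insulin dependence by a C-peptide cut-off. In the tablet arm, baseline HbA1c and treatment at entry help to decide where a patient starts on the treatment ladder. Baseline C-peptide could therefore help to predict HbA1c change, baseline HbA1c could help to predict C-peptide change, and entry treatment could help with both.

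What is at stake is precision. A prognostic baseline variable left out of a linear model leaves its share of variance in the residual, and the confidence interval is wider than it need be. C-peptide has the most to gain, because its power is the lower of the two at the planned size.

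A smaller matter is that *or* can also be read as leaving the choice of baseline open in each model.

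**Working it through.** **Inputs, all from Sample size unless noted**
- HbA1c: "To find a difference of 0.7% in average HbA1c (standard deviation = 1.5" per cent), a difference of 0.7% with SD 1.5%.
- C-peptide: difference 0.2 nmol/l; SD 0.5 nmol/l, from the cited 12-month study in China.
- Error rates: "power 90%, significance = 5" per cent; the Analysis plan adds "We shall use two sided tests and confidence intervals for all comparisons".
- Size: "we would need 97 analysible people in the insulin and the standard care arms of the study".
- Partial R² of the added covariates, given those already planned: not in the documents. Assumed range 0 to 0.15.

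**1. Reproduce the plan's figure**

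n per arm = 2 × SD² × (1.960 + 1.282)² / difference² = 2 × 2.25 × 10.507 / 0.49 = 96.5, rounded up to 97. The stated number reproduces, per arm and two-sided. Read as a total, 97 would give only 63% power; a one-sided test would need 79 per arm.

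Power at 97 per arm = Φ(difference / (SD × √(2/97)) − 1.960), with √(2/97) = 0.1436:
- HbA1c: 0.7 / (1.5 × 0.1436) = 3.250, so Φ(1.290) = 90.1% (t-based 89.9%).
- C-peptide: 0.2 / (0.5 × 0.1436) = 2.786, so Φ(0.826) = 79.6% (t-based 79.2%).

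**2. Cost of the extra terms**

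The planned model has six parameters (intercept, treatment, GAD, age, sex, own baseline), leaving 194 − 6 = 188 residual degrees of freedom. One more baseline and two indicators for entry treatment leave 185. The expected variance inflation is (188 − 1)/(185 − 1) = 187/184 = 1.016. Break-even is at a partial R² of 1 − 184/187 = 0.016.

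**3. Gain**

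The residual SD is multiplied by √(1 − R²). The columns marked net also multiply it by √1.016 and use 185 degrees of freedom. All powers are t-based, at 97 per arm.

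| Partial R² (assumed) | C-peptide 0.2 nmol/l | C-peptide, net | HbA1c 0.7% | HbA1c, net |
|---|---|---|---|---|
| 0 | 79.2% | 78.5% | 89.9% | 89.4% |
| 0.05 | 81.2% | 80.5% | 91.3% | 90.8% |
| 0.10 | 83.2% | 82.6% | 92.6% | 92.2% |
| 0.15 | 85.2% | 84.7% | 93.9% | 93.6% |

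Before the cost in step 2, the equivalent sample size is 97/(1 − R²) = 102, 108 and 114 per arm for the last three rows, or about 5, 11 and 17 more patients per arm. If the extra terms explain nothing, the loss is less than one percentage point of power.

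**4. If the stated SDs are not residual SDs**

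Suppose the planned covariates already explain 20% (assumption). The residual variance is then 0.80 of the stated value, and power starts at 87.6% for C-peptide and 95.3% for HbA1c (normal approximation). A further 10% brings it to 0.80 × 0.90 = 0.72, and power to 90.7% and 96.9%. The gain is then 3.1 and 1.6 points, against 4.0 and 2.7 on the same approximation (79.6% to 83.6%, and 90.1% to 92.9% before rounding) when the stated SDs are taken as residual.

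**The case against.** The strongest case against raising this is that nothing in the plan is wrong. The regression is standard and already contains the outcome's own baseline, usually the strongest covariate. Randomisation means that a prognostic variable left out of a linear model does not bias the treatment estimate or inflate type I error, and the intervals already allow for chance imbalance. The gain rests on an assumed R² that may be close to zero, and for HbA1c it is small anyway. The article is also condensed, and its list may not be final. All of this stands as a limit on the point's weight. What remains is that the article does name the covariates, that the additions are cheap, and that one sentence also settles *or*.

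Three stronger readings are tempting, and the documents do not support them.

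- *Each model adjusts for its own baseline only.* A reader might infer this from the word *or*. The same sentence also lists GAD level, age and sex. The omission concerns the other outcome's baseline and entry treatment.
- *Stopping sulphonylurea distorts the baseline in a way that the planned model cannot handle.* The sentence on discontinuation stands in Step 1 of the tablet arm, and the insulin-arm text does not mention earlier tablets, so its reach across both arms is an inference. No document says how many patients enter on sulphonylurea or that a withdrawal effect would persist in a 24-month change. If the trouble were one common baseline slope, a simple additive factor would not cure it, since it shifts intercepts only.
- *Avoidable noise certainly remains in both comparisons.* No document gives the correlation of the omitted variables with either change once the planned covariates are in the model. A gain is plausible but not shown.

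**Conclusion.** The point holds as an optional gain in precision. On the natural reading of the Analysis plan, each primary model lacks the other outcome's baseline, and both lack treatment at entry. No stated figure becomes wrong: 97 per arm reproduces, and the planned treatment estimate remains valid.

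The gain runs from nothing to about 6 percentage points of power for C-peptide (79% to 85%) and from nothing to about 4 for HbA1c (90% to 94%), with break-even at a partial R² of about 0.016. This rests on three assumptions: the added terms explain 0% to 15% of residual variance, the SDs in Sample size are residual SDs of the planned model, and entry treatment is known in both arms. The last is inferred from the tablet-arm steps; the article does not state it for the insulin arm. The lower C-peptide power shows where precision is most useful, but it is a matter of sample size and is not caused by the covariate list.

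**What to change.** Replace the covariate wording in the Analysis plan with a sentence such as: *Both primary regressions include treatment, baseline fasting C-peptide, baseline HbA1c, baseline GAD level, age, sex and diabetes treatment at entry (diet only; metformin; sulphonylurea with or without metformin).* Three details should go with it.

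- Define entry treatment as what the patient was taking before randomisation, recorded in the same way in both arms. The tablet-arm starting step must not stand in for it, since that step exists in one arm only.
- State in advance how a sparse level is merged, using counts pooled over the arms, and where any other entry treatment is placed.
- Fix the list before unblinding. Because the article keeps the analyst blind until the analysis has been interpreted, the list should also be fixed before any comparison by coded group.

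The cost is a wording change and about 3 of some 190 degrees of freedom. It needs no further patients or laboratory tests, only a check that entry treatment is on file for the insulin arm.
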